## Research Protocol

- ☐ Once or twice
- ☐ A few times
- ☐ About once a day
- ☐ About twice or three times a day
- ☐ More than three times a day
- ☐ N/A

Over the past 6 weeks, how often would you say that your partner has accessed the sling surgery services (either online, in person, or other)?

- ☐ Not at all
- ☐ About once a week
- ☐ About twice a week
- ☐ Generally more than three times a week
- ☐ Daily
- ☐ N/A

Over the past six weeks, have you needed to swap your sling for a different one, and if so, how many times have you swapped slings?

- ☐ I have not swapped slings.
- ☐ Yes, I have swapped slings once.
- ☐ Yes, I have swapped slings twice.
- ☐ Yes, I have swapped slings three times.
- ☐ Yes, I have swapped slings more than three times.

### Mental Health (Access to Support) Items

**Overall, how would you rate your mental health currently?**

- ☐ Good
- ☐ Somewhat Good
- ☐ Average
- ☐ Somewhat Poor
- ☐ Poor

**Are you currently accessing support for any mental health difficulties? (e.g. medication, therapy, support groups etc.).**

- ☐ Yes
- ☐ No

If yes, would you mind saying what support you are accessing?

## Appendix C Edinburgh Post-natal Depression Scale

(EPDS; Cox, Holden & Sagovsky, 1987)

As you are pregnant or have recently had a baby, we would like to know how you are feeling. Please check the answer that comes closest to how you have felt **IN THE PAST 7 DAYS**, not just how you feel today.

Here is an example, already completed.

I have felt happy:

- ☐ Yes, all the time
- ☒ Yes, most of the time      This would mean: "I have felt happy most of the time" during the past week.
- ☐ No, not very often      Please complete the other questions in the same way.
- ☐ No, not at all

In the past 7 days:

- |                                                                                                                                                                                                                                                                                                                                                                                                                                                                                                                                                                                                                                                                                                                                                                                                                                                                                                                                                                                                                                                                                                                                                                                                                                                                                                                                                                                                                                                                                                                                                                                                            |                                                                                                                                                                                                                                                                                                                                                                                                                                                                                                                                                                                                                                                                                                                                                                                                                                                                                                                                                                                                                                                                                                                                                                                                                                                                                                                                                                                                                                                                                                                                                                                                                                              |
|------------------------------------------------------------------------------------------------------------------------------------------------------------------------------------------------------------------------------------------------------------------------------------------------------------------------------------------------------------------------------------------------------------------------------------------------------------------------------------------------------------------------------------------------------------------------------------------------------------------------------------------------------------------------------------------------------------------------------------------------------------------------------------------------------------------------------------------------------------------------------------------------------------------------------------------------------------------------------------------------------------------------------------------------------------------------------------------------------------------------------------------------------------------------------------------------------------------------------------------------------------------------------------------------------------------------------------------------------------------------------------------------------------------------------------------------------------------------------------------------------------------------------------------------------------------------------------------------------------|----------------------------------------------------------------------------------------------------------------------------------------------------------------------------------------------------------------------------------------------------------------------------------------------------------------------------------------------------------------------------------------------------------------------------------------------------------------------------------------------------------------------------------------------------------------------------------------------------------------------------------------------------------------------------------------------------------------------------------------------------------------------------------------------------------------------------------------------------------------------------------------------------------------------------------------------------------------------------------------------------------------------------------------------------------------------------------------------------------------------------------------------------------------------------------------------------------------------------------------------------------------------------------------------------------------------------------------------------------------------------------------------------------------------------------------------------------------------------------------------------------------------------------------------------------------------------------------------------------------------------------------------|
| 
1. I have been able to laugh and see the funny side of things
 

 As much as I always could

 Not quite so much now

 Definitely not so much now

 Not at all

 
2. I have looked forward with enjoyment to things
 

 As much as I ever did

 Rather less than I used to

 Definitely less than I used to

 Hardly at all

 
*3. I have blamed myself unnecessarily when things went wrong
 

 Yes, most of the time

 Yes, some of the time

 Not very often

 No, never

 
4. I have been anxious or worried for no good reason
 

 No, not at all

 Hardly ever

 Yes, sometimes

 Yes, very often

 
*5. I have felt scared or panicky for no very good reason
 

 Yes, quite a lot

 Yes, sometimes

 No, not much

 No, not at all

 | 
*6. Things have been getting on top of me
 

 Yes, most of the time I haven't been able to cope at all

 Yes, sometimes I haven't been coping as well as usual

 No, most of the time I have coped quite well

 No, I have been coping as well as ever

 
*7. I have been so unhappy that I have had difficulty sleeping
 

 Yes, most of the time

 Yes, sometimes

 Not very often

 No, not at all

 
*8. I have felt sad or miserable
 

 Yes, most of the time

 Yes, quite often

 Not very often

 No, not at all

 
*9. I have been so unhappy that I have been crying
 

 Yes, most of the time

 Yes, quite often

 Only occasionally

 No, never

 
*10. The thought of harming myself has occurred to me
 

 Yes, quite often

 Sometimes

 Hardly ever

 Never

 |
|------------------------------------------------------------------------------------------------------------------------------------------------------------------------------------------------------------------------------------------------------------------------------------------------------------------------------------------------------------------------------------------------------------------------------------------------------------------------------------------------------------------------------------------------------------------------------------------------------------------------------------------------------------------------------------------------------------------------------------------------------------------------------------------------------------------------------------------------------------------------------------------------------------------------------------------------------------------------------------------------------------------------------------------------------------------------------------------------------------------------------------------------------------------------------------------------------------------------------------------------------------------------------------------------------------------------------------------------------------------------------------------------------------------------------------------------------------------------------------------------------------------------------------------------------------------------------------------------------------|----------------------------------------------------------------------------------------------------------------------------------------------------------------------------------------------------------------------------------------------------------------------------------------------------------------------------------------------------------------------------------------------------------------------------------------------------------------------------------------------------------------------------------------------------------------------------------------------------------------------------------------------------------------------------------------------------------------------------------------------------------------------------------------------------------------------------------------------------------------------------------------------------------------------------------------------------------------------------------------------------------------------------------------------------------------------------------------------------------------------------------------------------------------------------------------------------------------------------------------------------------------------------------------------------------------------------------------------------------------------------------------------------------------------------------------------------------------------------------------------------------------------------------------------------------------------------------------------------------------------------------------------|

Appendix D Ten-point Supplement to EPDS Manual (Cox, Holden & Henshaw, 2014)

**When using the EPDS for clinical or research purposes, give very careful consideration to the following ten points:**

1. Be careful to check the validity of the scale for the population of mothers completing the EPDS.
2. Establish its sensitivity, specificity, positive predictive value and optimal cut off points for the purpose of your clinical or research work.
3. Remember that the EPDS is NOT diagnostic of mental disorder. A 'high score' indicates that depressive symptoms are present—but not their duration or intensity. The EPDS is not a test for PND or for an anxiety disorder.
4. When using the EPDS in other languages, make sure that the back translation is satisfactory and that there is also evidence of satisfactory Face, Semantic, Conceptual and Technical validity.
5. Remember that the EPDS is NOT a check list of common symptoms of perinatal depression. It deliberately omitted somatic symptoms and items concerned with the mother-infant relationship.
6. Remember that the EPDS was validated, piloted and evaluated in Edinburgh by a clinically informed research team to assist with the detection of postnatal and antenatal depression in community clinics.
7. When using the EPDS as an aid to assessment, or in universal or targeted screening, remember that its administration must be supervised by a trained health professional with access to mental health services.
8. When used to assess a mother in the community, the practitioner should discuss the responses with her, listen to her story, ascertain whether clinical depression or another mental disorder is present—and consider referral and/or further listening visits.
9. The risk of developing a postnatal psychosis should always be assessed. The EPDS does NOT screen for bipolar disorder.
10. The EPDS was developed in Edinburgh by John Cox, Jenifer Holden and Ruth Sagovsky over thirty years ago. Please read the recent EPDS Manual (Cox et al. [2014](#)) so that the scale continues to be used optimally in research and clinical work.

## Appendix E EPDS: Postnatal Depression Threshold Letter

**The EPDS is not a diagnostic tool, but it is a screening tool which is designed to identify women who may benefit from further assessment or follow-up care (Cox, Holden & Sagovsky, 1987).**

**According to the EPDS instructions, a score of 13 or higher on this measure indicates a high likelihood of depression. As such, it is recommended that the person access primary care services for further assessment.**

**This letter will be sent to women who achieve a score of 13 or more when completing the EPDS at any time point.**

Dear [insert name],

You recently completed a set of questionnaires as part of your participation in the Sling Provision and Maternal Wellbeing study.

On one of the questionnaires, the Edinburgh Postnatal Depression Scale, the score you have suggests that you may be feeling low, tired or worried, following the birth of your child. It may be that you are suffering from postnatal depression, which is very common among families and underdiagnosed. There is help available if you are feeling this way. We recommend that you contact your GP, midwife or health visitor, to talk about these experiences, and seek further support.

Whatever you decide to do, whether you contact your GP, midwife or health visitor, or not, this will not impact on your participation in this study.

If you feel that at this point you would like to withdraw from the study, please feel free to do so, but please let us know by emailing the address below.

[[contact]](mailto:[contact])

Thank you and best wishes,

[name] and [name].

Sling Use and Maternal Wellbeing Project,

University of Sheffield.

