### *Postnatal Depression*

Our primary measure is the Edinburgh Postnatal Depression Scale (EPDS; Cox, Holden & Sagovsky, 1987)(Appendix C) . The EPDS is a 10 item self-report scale designed to screen for postnatal depression in nonclinical populations. Participants give one of four possible responses to each of the ten statements. These possible responses indicate frequency, e.g. ranging from “Not at all” to “Yes, most of the time”, but the exact wording varies according to the statement. The scale typically takes around 5 minutes to complete (Cox et al., 1987).

The EPDS has been used widely in the National Health Service (NHS) as a screening tool for post-natal depression; and in previous studies in the field of maternal mental health and wellbeing (Leahy-Warren, McCarthy & Corcoran, 2012). A number of past studies found this scale to be a valid and reliable (Cox & Holden, 1994; Pope & Pope, 2000). In 2017, Cox published a 10 point supplement to their previous manual for this scale, designed to assist researchers in avoiding misuse of the EPDS (Cox, 2017). This study aims to follow both the manual for the scale (Cox, Holden & Henshaw, 2014), and this supplement (see Appendix D), in order to ensure standardised practice.

Because this measure is the primary screening tool for PND used in the NHS, if a participant scores above the clinical threshold implemented in the NHS, they will be sent a letter informing them of this, and encouraging them to access assessment and treatment for

postnatal depression via their GP or health visitor. This letter can be found in Appendix E.

At all three data collection time-points, information will be collected around whether participants are currently accessing pharmacotherapy or psychological care, using specific mental health-related items (please see Appendix B). This is in order to control for this variable during data analysis.

Recent studies have found that the sensitivity and specificity of the EPDS can vary between 59% to 100% and 44% to 97% (respectively) according to the geographic location of the study, the cutoff scores chosen by researchers, and the reference standards used for diagnosis (Novotney & Maurer, 2017).

Due to this variability in terms of sensitivity and specificity, some studies have recommended supplementing the EPDS with a second validated measure of depression that has shown less variation in sensitivity and specificity (Miller, Pallant, & Negri, 2006).

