## Research Protocol

- ☐ From advertising in a baby care shop
- ☐ From advertising in a library
- ☐ Via a church/church-run group
- ☐ From advertising in a café
- ☐ From advertising in a soft play centre
- ☐ From advertising in a sports/yoga centre
- ☐ From advertising in a private health clinic (e.g. chiropractors, physiotherapists)
- ☐ Via an online group (Mumsnet, facebook, Instagram etc.)
- ☐ Via the Sheffield Sling Surgery
- ☐ Other

If other, please state here: .....

Due date:

Email address:

Telephone number (mobile):

Generally, I would prefer to be contacted by:

- ☐ Email
- ☐ Text
- ☐ Both email and text

Thank you very much for agreeing to participate in this study. You will now receive an email with information about what happens next.

Aside from this email, and contact from the Sling Surgery, we will aim to contact you via your preferred method, as indicated by yourself above.

If you have any questions at this stage, please do not hesitate to contact us on:

[[contact]](mailto:[contact])

If you did not mean to consent to participate in the study, please contact us on the above email address to let us know, and we will remove your information immediately.

Thank you and best wishes,

[name] (Trainee Clinical Psychologist) and [name] (Lecturer in Psychology and Project Supervisor)

University of Sheffield.

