### **What will happen to the data collected?**

Any questionnaire data collected from you has been anonymised. This data is stored securely and is only available to members of the research team, including staff from the Sheffield Sling Surgery. Sheffield Sling Surgery will retain your contact details until after you have returned the sling you received under a free hire arrangement as part of this project, at which point, you can request that this information be destroyed. The University of Sheffield will destroy your contact details after sending you this debriefing sheet. Your contact details are not linked in any way to the questionnaire data you have provided, so you cannot be identified within the aggregated set of responses.

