| Postage Include:
- cost of outward postage (NB: varies according to size/weight – check with Royal Mail) e.g. 200 2 nd class letters @ [amount each] for outward mailing
- Freepost envelopes, plus cost of return postage for the number of estimated returns

20 1 st Class signed for letters @ £1.77 each for outward mailing.

This more expensive postage option has been selected for ethical reasons, as it is for letters that will be sent in response to participants who have scored as likely to be suffering from postnatal depression, recommending that they contact their GP/Midwife/Health Visitor. | £35.40 |
| subtotal                                                                                                                                                                                                                                                                                                                                                                                                                                                                                                                                                                                                                                                                    | £35.40 |

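### The posted letter promised for an EPDS score of 13 or more is not supported by the contact-detail and retention rules shown, most clearly for a score at T3

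*Protocol*

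**What the plan says.** **The promise.** Protocol, Measures, Postnatal Depression: "if a participant scores above the clinical threshold implemented in the NHS, they will be sent a letter informing them of this". Ethical Implications repeats the commitment and has the letter marked as private. Appendix E sets the trigger: "This letter will be sent to women who achieve a score of 13 or more when completing the EPDS at any time point".

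**The route.** It is paper mail. Justification for Proposed Costs covers the printing of the letters, and Appendix Y budgets 20 printed sheets, 20 envelopes and 20 first "Class signed for letters @ £1.77 each for outward mailing".

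**The contact data.** Appendix S.2, described as the page on which participants give contact details after consenting, asks for name, how they heard of the study, due date, email, mobile number and preferred channel (email, text or both). Appendix O asks for a postcode at T1. Sign-in at the Sling Surgery (Procedure, Intervention) takes name, email and postcode.

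**The retention rule.** Under Procedure, Debrief, completing T3 triggers the debrief email. The attached sheet (Appendix V) says: "The University of Sheffield will destroy your contact details after sending you this debriefing sheet". It adds: "Your contact details are not linked in any way to the questionnaire data you have provided".

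**The scale's own guidance.** Of the EPDS manual and the ten-point supplement, the Postnatal Depression section says: "This study aims to follow both the manual for the scale", and it names the supplement alongside. Appendix D, point 7, asks users of the scale to "remember that its administration must be supervised by a trained health professional with access to mental health services".

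**The concern.** A signed-for letter needs a postal address, and a letter triggered by a score needs a link between that score and a named person. The forms shown do not supply the first, and the debrief sheet denies the second. At T3 there is also a question of order: the debrief goes out on submission, deletion follows the debrief, and nothing says the EPDS must be scored and any letter posted before deletion.

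At stake is whether a woman who screens positive at the last time point receives the letter promised to her, and whether a statement made to every participant who completes T3 is true of the plan. No estimate or feasibility outcome depends on it.

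**Working it through.** **1. The plan's own figures.** Postage: 20 × £1.77 = £35.40, as stated. Total: £1.00 + £35.40 + £73.10 + £80 = £189.50, as stated. The arithmetic is right and confirms that paper post is the intended route.

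**2. Address data, form by form.**

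| Source | Contact or address items |
|---|---|
| Appendix S.2 | Name, email, mobile |
| Appendix O (T1) | Postcode |
| Sling Surgery sign-in | Name, email, postcode; controls are invited only after T3 |
| Appendices Q and R | Not visible |

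No visible form yields a full postal address.

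**3. Order of events at T3.** T3 is submitted; the debrief email is triggered; contact details are deleted at some unstated time after that. The T3 EPDS must be scored and any letter sent somewhere in this sequence, but no step is tied to them. T1 and T2 letters are not touched by the deletion rule.

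**4. The non-linkage sentence against the rest of the protocol.**
- Appendix E: a letter addressed by name because of a score needs the link.
- Data Security and Management: identifiable data are kept, and the analysis depends on matching each woman's records across time points.
- Ethical Implications and Appendix S.5: data can be withdrawn at any time, and on an emailed request, which again needs the link.

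The deletion sentence also sits badly with Appendices S.13 and S.14, which promise controls a later email or text when the four-week sling hire ends.

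**5. How often the T3 case would arise.** Inputs: N = 50–60 (Sample Size); p = 10–15% (Introduction). The p is a prevalence of postnatal depression, used here only as an assumed rate of scoring 13 or more. Full follow-up is assumed, and independence between women for the probability.

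| N | p | T3 letters, N × p | All letters, 3 × N × p | P(at least one at T3) = 1 − (1 − p)^N |
|---|---|---|---|---|
| 50 | 0.10 | 5.0 | 15.0 | 0.9948 |
| 50 | 0.15 | 7.5 | 22.5 | 0.9997 |
| 60 | 0.10 | 6.0 | 18.0 | 0.9982 |
| 60 | 0.15 | 9.0 | 27.0 | 0.9999 |

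The range of 15 to 27 letters straddles the 20 budgeted. The midpoint is 3 × 55 × 0.125 = 20.6.

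**The case against.** Several stronger readings are tempting, and the documents do not carry them.

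- **That no address is collected, so no letter can be posted.** Procedure points to appendices that include the information sheet and consent form for consent and contact details, and those pages are not visible. Emails and mobile numbers are held, so women remain reachable. What stands is that the page described as the contact form has no address field, and that no electronic route for the letter is stated.
- **That details are gone before a T3 letter can be sent.** Appendix V says after sending, with no interval, and the sling-return reminder shows that some later contact is expected. What stands is that nothing makes deletion wait for scoring and the letter.
- **That women who screen positive would get no response at all.** Appendix S.6 directs women to their GP at every time point, and the debrief sheet names the GP or health visitor. The letter is the only response triggered by a score, which is a narrower statement.
- **That the supplement forbids this use.** Points 7 and 8 are conditional on the purpose of use, and the protocol only aims to follow the supplement. But the protocol also describes the EPDS as a screening tool and uses it to flag women from online self-completion, so the sections still need reconciling.
- **That the postage budget is too small.** The range above includes the 20 letters costed, so no shortfall is shown.

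Two further points soften the contradictions. The non-linkage sentence could describe the position once the study is over, with the matching done earlier. But the sheet goes out automatically at T3 completion, when the T3 score may still call for a letter, so the sentence is at best premature. And the debrief sheet lets the Sling Surgery keep its own copy of contact details, so the sling-return reminder could come from there. Against that, the emails ask controls to tell the principal investigator which channel they prefer, which suggests that the research team sends it.

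**Conclusion.** The concern holds in a limited form. The plan promises a posted, score-triggered letter at every time point, but no form shown collects the address it needs. The debrief sheet's deletion and non-linkage statements conflict with a letter owed for a T3 score, and the non-linkage statement also conflicts with withdrawal of data on request. On the assumed 10–15% rate, 5 to 9 women would be affected at T3, and at least one almost certainly, so the gap would be met in practice.

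The address point is conditional on the unseen consent pages. The T3 conflict and the non-linkage contradiction rest on visible text alone. The size rests on using a prevalence as a rate of EPDS scores of 13 or more, with full follow-up. Nothing here bears on randomisation, outcomes or analysis. It deserves correction because it concerns women flagged for likely depression and the remedy is very cheap.

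**What to change.** 1. Add a postal-address field to Appendix S.2, or confirm that the consent form already has one, or state an electronic route for the letter.
2. Reword the deletion sentence in Appendix V so that contact details and the link to the answers are kept until the T3 EPDS has been scored, any letter has been sent, and promised follow-up contact is complete.
3. Replace the non-linkage sentence in Appendix V with one that describes accurately when and how data are separated from identity, consistent with Data Security and Management and with the right to withdraw.
4. Reconcile Measures (Postnatal Depression), Ethical Implications and Appendices D and E on how EPDS responses are handled. Which procedure applies is for the clinical team.

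Cost of items 1 to 3: one form field, two debrief sentences and an ethics notification. Item 4 needs a short clinical decision and matching text. No change to sample size or analysis is needed.
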